**Background**

Antimicrobial resistance is a globally recognised public health threat, and one of its primary drivers is the significant increase in antibiotic prescriptions. In China, the use of antibiotics is common in rural areas. Acute respiratory infections (ARIs), which include symptoms such as coughing and fever, are among the primary reasons for antibiotic prescriptions in village clinics. However, only a small proportion of patients with bacterial ARIs actually require antibiotic treatment. Identifying effective interventions to reduce the inappropriate use of antibiotics for ARIs in village clinics could significantly improve antibiotic use in China. In recent years, certain biomarkers, such as C-reactive protein (CRP), have increasingly been utilised to inform antibiotic prescribing practices for ARIs. Although CRP POCT is a valuable tool in diagnosing bacterial infections, its specificity is limited, as viral infections can also lead to elevated CRP levels. Additionally, since CRP is part of a dynamic and continuous inflammatory process, a single CRP measurement, especially at low concentrations, may erroneously classify an infection as viral rather than bacterial, potentially delaying appropriate antibiotic treatment. The clinical significance of serum amyloid A (SAA) is promising as changes in its levels play a crucial role in the early diagnosis of infectious diseases. SAA demonstrates high diagnostic accuracy for viral infections and is significantly elevated during the acute phase of such infections. By assessing the degree of SAA and combining it with CRP, it is possible to differentiate between bacterial and viral infections more accurately. This indication of a combined biomarker addresses the limitations of currently used single biomarkers, which often fail to indicate viral infections specifically. Despite its significant potential, the evidence supporting the use of CRP&SAA POCT for antibiotic management of ARIs in primary care settings remains insufficient. The simplicity, rapidity, low cost, and high accuracy of CRP&SAA POCT make it particularly suitable for remote primary healthcare settings, such as village clinics in China.

**Methods****Design**

This is a pragmatic, parallel-group, cluster randomised controlled trial designed to evaluate the impact of a CRP&SAA POCT-based comprehensive intervention on

antibiotic prescribing for patients with ARIs in Chinese village clinics. This study will be conducted over a period of six months across 40 village clinics, with randomization stratified by township. CRP&SAA POCT will be implemented in 20 village clinics within the intervention arm. This will include additional training for village doctors on the operations of CRP&SAA POCT, which encompasses centralised training, the distribution of training manuals, and desk reminders. The aim is to help village doctors understand the significance of CRP&SAA POCT in guiding antibiotic prescriptions and to familiarise them with the specific operational procedures. Additionally, patient education materials will be provided to assist patients in understanding how CRP&SAA POCT can aid in their diagnosis and treatment. The control arm will not receive any intervention and will continue with usual care.

### **Aims and hypotheses**

In this study, we aim to evaluate the effectiveness of a comprehensive intervention based on CRP&SAA POCT, which we hypothesised would reduce the inappropriate use of antibiotics for ARIs in Chinese village clinics.

### **Setting**

As the primary providers of health care services in rural China, village clinics address various aspects, including basic medical services, preventive health care, public health services, and drug supply, with the goal of meeting the fundamental medical and public health needs of rural residents. This study will be conducted in 40 village clinics across 15 townships and 4 sub-district offices (equivalent to townships) in Xiantao, Hubei Province. Xiantao is situated in central China's Hubei Province, with a population of approximately 1.11 million permanent residents. The city administers 15 townships and 4 sub-district offices. Each village clinic employs 1 to 2 upgraded community health workers, commonly referred to as 'village doctors'. All village doctors have successfully passed the national doctor qualification examination and have obtained either a certificate of practicing physician qualification or a certificate of practicing assistant physician qualification. This includes qualifications for practicing as a physician or assistant physician in the clinical category, as well as the rural general practice assistant physician qualification.

### **Intervention**

According to national and international guidelines, the self-limiting virus ARIs should not be treated with antibiotics. The intervention aimed to guide the prescribing behavior of ARIs by doctors in Chinese village clinics through the use of CRP&SAA POCT. The purpose and design of this study adhered to policy requirements for antibiotic prescribing and are subject to routine oversight by local health authorities. To facilitate the implementation of CRP&SAA POCT, the intervention design is guided by the Theoretical Domain Framework (TDF), an emerging approach developed from a diverse array of theories related to behavior change. The TDF comprises 14 theoretical domains and is widely utilised in implementation studies to

design interventions and examine factors that influence their effectiveness. Several theoretical areas within the TDF were identified as crucial for CRP&SAA POCT-guided antibiotic prescribing, where the content of relevant behavior change techniques and interventions was specifically targeted.

#### *CRP&SAA POCT*

Serum Amyloid A/C-Reactive Protein Combined Assay Kit (Immunochromatography) will be supplied to all village clinics in the intervention arm for the target population (ARIs patients). Since the purpose of this study is to determine whether antibiotic prescribing for ARIs can be guided by the use of CRP&SAA POCT, the intervention arm should be encouraged to utilise CRP&SAA POCT for all target populations (patients with ARIs). This recommendation is suggested but not mandated. The control arm will not receive any intervention (usual care). Village doctors will decide whether to prescribe antibiotics to patients with ARIs based on the recommended threshold for CRP&SAA levels (mg/L). As there is currently no specific cut-off threshold for CRP and SAA, our recommended threshold was developed in conjunction with previous studies and expert consensus in China to align more closely with clinical practice. In order to further encourage village doctors to utilise CRP&SAA POCT, we simulated real-world conditions. According to the reimbursement policy, the Rural Cooperative Medical Care in China, provides a 60% reimbursement for visits to village clinics. Each patient with an ARI utilizing the CPR&SAA POCT, originally priced at 14 yuan (approximately US \$1.92), will ultimately pay 5 yuan (approximately US \$0.68) to the village clinic.

#### *Healthcare worker training*

After randomization, we will implement a unified and centralised training program for doctors in all village clinics within the intervention arm. The training will cover the following topics: (1) the operation process for CRP&SAA POCT; (2) recommended thresholds for CRP&SAA, along with practical case applications; and (3) clinical evaluation and management of ARIs. Following the intensive training, the research team will provide on-site guidance for the use of CRP&SAA POCT in each village clinic within the intervention arm for one week. This support will ensure that each village doctor is capable of independently operating the CRP&SAA POCT. Training will be conducted by the research team, and an online communication group will be established to address any questions that village doctors may have during the follow-up process. The research team will distribute a CRP&SAA POCT-based village clinic guidance manual on the rational use of antibiotics for ARIs to each village clinic in the intervention arm. This guideline includes an introduction to ARIs, standardised procedures for their diagnosis and treatment, CRP&SAA POCT-based clinical diagnosis and treatment pathways for ARIs, a brief overview of the principles of CRP&SAA POCT, and illustrated operational steps. Desktop reminders featuring the recommended thresholds from CRP&SAA will be distributed to the intervention arm. Village doctors in the intervention arm will be informed that the CRP&SAA recommended threshold serves only as a suggestion, and that antibiotic prescribing

must ultimately be determined based on the clinical judgment. If a village doctor believes that patients with ARIs require referral to a higher level of care, the referral should be done immediately, and CRP&SAA POCT should not be utilised. At the beginning of each month following the intervention, the research team will gather prescription information for ARIs from all village clinics within the intervention arm. The team will conduct a comprehensive assessment to determine whether village doctors are prescribing antibiotics in accordance with the CRP&SAA POCT threshold. Subsequently, the team will provide feedback to the relevant village clinics and administrative staff.

#### *Patient education*

For the village clinics in the intervention arm, patients presenting with ARIs will receive a popular science leaflet detailing the role of CRP&SAA POCT in promoting the rational use of antibiotics for ARIs, as well as the risks associated with antibiotic overuse. According to the information provided in the publicity leaflet and the advice of the village doctor, patients with ARIs (or their legally appointed agents) will determine whether to consent to CRP&SAA POCT based on their individual circumstances.

#### **Usual care**

Village clinics in the control arm will continue to prescribe antibiotics to patients with ARIs in accordance with the current national guidelines and usual care in village clinics. In usual care, village doctor will diagnose and treatment of ARIs based on their clinical experience and existing knowledge, and make decision on whether to prescribe antibiotics. Notably, the village doctors in the control arm will not receive any education on ARIs and the appropriate use of antibiotics, and will not receive the Serum Amyloid A/C-Reactive Protein Combined Assay Kit.

#### **Allocation and blinding**

The 40 village clinics will be randomly assigned to one of the two arms, stratified by township, to prevent any imbalance in distribution among townships, while considering potentially significant variation in outcomes between townships. Randomisation will be conducted using R version 4.0.5 (R Foundation for Statistical Computing). ARIs patients and village doctors will not be blinded to the treatment; however, measures will be implemented to ensure a blinded outcome evaluation by employing the 'PROBE' design.

#### **Eligibility**

##### *Eligibility criteria for clusters*

Village clinics with an annual outpatient volume exceeding 2000, an average of 10 or more patients per week presenting with ARIs, and licensed prescribers are considered eligible for selection for the intervention. Annual outpatient prescriptions and average weekly visits for ARIs will be verified by obtaining prescription data from all village

clinics for the previous year, as documented in the information section of the local health board.

#### *Eligibility criteria for participants*

The target population of this study included (1) patients of all ages diagnosed by a village doctor with ARIs (including upper and lower respiratory infections); and (2) patients who present with  $\geq 1$  acute respiratory symptoms (including cough, rhinitis (sneezing, nasal congestion or runny nose), sore throat, shortness of breath, wheezing or abnormal auscultation). Patients with non-respiratory diseases or those with severe clinical symptoms requiring referral to a higher-level institution are excluded from the target population.

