### **Outcomes**

#### *Primary outcome*

The primary outcome is the proportion of patients who are diagnosed with ARIs and prescribed antibiotics during their initial visit (defined as no prescription record at the current institution within the preceding 14 days) in both study arms. This outcome serves as the primary indicator, reflecting the overall impact of a comprehensive intervention based on CRP&SAA POCT in guiding antibiotic use for patients with ARIs. Since most self-limiting ARIs are caused by viral infections that do not require antibiotic treatment, the decline in antibiotic prescribing rates suggests that village doctors are prescribing antibiotics more judiciously. The selection of this outcome is both feasible and reliable within the context of village clinics in China. This is due to the transition of prescriptions from traditional paper documents to electronic storage, which allows for the proper preservation of prescription records, thereby ensuring data integrity and traceability.

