### **Data analysis plan**

All analyses will be conducted on the intention-to-treat (ITT) population, defined as all outpatient prescriptions issued by village clinics for ARI patients, regardless of the compliance of village doctors and patients with the intervention. For the primary and secondary outcomes, which are binary variables, we will employ Generalised estimating equations (GEEs) to estimate both relative and absolute measures of effect. The same methods will be used to analyse the mean cost of an ARI prescription and a consultation. The primary outcome will also be analysed in subgroups based on ARI

patient's age (1-15 / 16-65 / over 65 years old), ARI patient's sex (male / female), type of ARI (upper respiratory tract infection / lower respiratory tract infection), and season. Likelihood ratio tests will be employed to assess the heterogeneity of antibiotic prescribing across these different subgroups. We also will conduct per-protocol analyses, which included only ARI patients who received CRP&SAA POCT in village clinics within the intervention arm. Furthermore, modified poisson regression and linear regression models, which account for village-level clustering using the clustered sandwich estimator, will be employed to replicate all results and assess their robustness. No interim analyses are planned, and all outcomes will be analysed following data collection.

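### Entry to the primary denominator is an ARI diagnosis made after randomisation by unblinded doctors who are trained, equipped and audited in one arm only, and no analysis in the Protocol checks for differential labelling

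*Protocol*

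**What the plan says.** *Case definition.* Protocol, Eligibility criteria for participants, defines the target population as "patients of all ages diagnosed by a village doctor with ARIs (including upper and lower respiratory infections", together with at least one listed acute respiratory symptom or sign. It adds: "Patients with non-respiratory diseases or those with severe clinical symptoms requiring referral to a higher-level institution are excluded from the target population". No assessor other than the village doctor is named for any of these judgements.

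*Outcome and population.* The primary outcome is "the proportion of patients who are diagnosed with ARIs and prescribed antibiotics during their initial visit". The Data analysis plan defines the intention-to-treat population as outpatient prescriptions for ARI patients, so both are conditional on the label.

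*Timing and blinding.* Training is placed after allocation: "After randomization, we will implement a unified and centralised training program for doctors in all village clinics within the intervention arm". Allocation and blinding states that "ARIs patients and village doctors will not be blinded to the treatment", and offers instead that "measures will be implemented to ensure a blinded outcome evaluation by employing the 'PROBE' design".

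*Differences between arms.* Healthcare worker training gives intervention doctors instruction in evaluating and managing ARIs. Each month the research team collects their ARI prescriptions and assesses whether prescribing agreed with the CRP&SAA threshold, after which "the team will provide feedback to the relevant village clinics and administrative staff". The test kits go to the intervention arm for ARI patients. Under Usual care, control doctors receive no ARI education and no kits.

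*Subgroup.* The primary outcome is also to be analysed by "type of ARI (upper respiratory tract infection / lower respiratory tract infection", with a likelihood ratio test for heterogeneity.

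**The concern.** In a cluster trial with open allocation, a denominator recorded by the treated clinicians is itself a post-randomisation variable. Training, a test reserved for one diagnosis, and audit of prescriptions under that diagnosis can each change how readily a doctor records it. No bad faith is needed: learning to recognise ARIs better would be enough.

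The primary proportion can then move while the antibiotics dispensed stay the same. If antibiotic-treated patients are recorded under another diagnosis, or more mild untreated patients are recorded as ARI, the intervention rate falls. The opposite pattern would hide a real effect. The secondary outcomes come from the same prescriptions, and the 30-day hospitalisation indicator has the same denominator, so added mild cases would also dilute the safety rate.

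The safeguards in the Protocol act at a different point. Blinded evaluation governs how the outcome is read once the patient is in the data set. Electronic records preserve the diagnosis that was entered but do not make it independent of allocation.

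**Working it through.** **1. The plan's own figure (Protocol, Sample size).** Inputs: 50% versus 37.5%, 90% power, two-sided 5%, cluster size 500, intracluster correlation 0.05, 15% data loss.
- Individually randomised size: 329 per arm (pooled variance) or 325.7 (unpooled).
- Design effect: 1 + 499 × 0.05 = 25.95.
- Clinics per arm: 329 × 25.95 / 500 = 17.08, or 325.7 × 25.95 / 500 = 16.91. The stated figure is 17.
- Data loss: 17 / 0.85 = 20.

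The sample size reproduces and is not in dispute. The planned difference is 50 − 37.5 = 12.5 points.

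**2. Effect of relabelling with no change in prescribing.** Let *p* = 0.50 be the true rate in both arms. The shares *f* and *g* are assumptions; the Protocol gives no such figures.

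*Coding out:* a share *f* of true ARI cases, all treated, is recorded under another diagnosis. Apparent rate = (*p* − *f*)/(1 − *f*).
- *f* = 5%: 0.45/0.95 = 47.4%, a fall of 2.6 points.
- *f* = 10%: 0.40/0.90 = 44.4%, a fall of 5.6 points.
- *f* = 20%: 0.30/0.80 = 37.5%, the whole planned effect.

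*Coding in:* extra untreated visits, *g* per true ARI case, are recorded as ARI. Apparent rate = *p*/(1 + *g*).
- *g* = 10%: 0.50/1.10 = 45.5%, a fall of 4.5 points.
- *g* = 20%: 0.50/1.20 = 41.7%, a fall of 8.3 points.
- *g* = one third: 37.5%.

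These are upper bounds for each share, because every case coded out is taken as treated and every case coded in as untreated. If only 75% of those coded out were treated, *f* = 10% gives (0.50 − 0.075)/0.90 = 47.2%, a fall of 2.8 points. If 25% of those coded in were treated, *g* = 10% gives (0.50 + 0.025)/1.10 = 47.7%, a fall of 2.3 points.

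**3. Consequence for the test.** With 20 clinics per arm, 500 per clinic and the planned correlation, the chance of a significant false benefit under full coding out is about 11% at *f* = 5% and 34% at *f* = 10%.

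**4. Do the analyses named in the Protocol reach this?** The GEE models, the subgroups, and the modified Poisson and linear regression replications all use ARI-labelled records. The per-protocol analysis narrows these further, to tested patients in the intervention arm. None examines entry into the label.

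**5. Subgroup.** Assume 1,000 cases: 800 upper (360 treated, 45%) and 200 lower (140 treated, 70%). Relabel 50 treated upper cases as lower. Upper becomes 310/750 = 41.3% and lower 190/250 = 76.0%, while the overall rate stays at 500/1,000 = 50%. Relabelling between upper and lower disturbs the subgroup comparison but not the primary outcome.

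**6. What an all-visit denominator can show.** At the cluster eligibility minimums (10 ARI patients a week, 2,000 outpatient visits a year), the ARI share is 10 × 52 / 2,000 = 26%. The planned effect over all visits is 12.5 × 0.26 ≈ 3.3 points. Relabelling alone moves this measure by zero, since neither the antibiotics nor the visits change. The ARI share itself would move from 26% to 26 × 0.9 = 23.4% with 10% coded out, or to 26 × 1.1 = 28.6% with 10% coded in. If both happened together the share would stay at 26% while the apparent rate fell to (0.50 − 0.10)/1.00 = 40%. Volume alone is therefore not a sufficient check.

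**The case against.** Several points on the other side are fair.

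- *The audit.* A reader might infer that doctors are judged on their ARI antibiotic rate. The Protocol does not say so. The audit concerns agreement with the CRP&SAA threshold, the threshold is described as advisory, testing is not mandatory, and no sanction or target is stated. Only discordant antibiotic prescriptions carry an audit reason for recoding, so that route is narrower than it first looks. It remains open, as do the routes through training and through the test itself.
- *The symptom criterion.* Requiring a respiratory symptom as well as the diagnosis limits coding in. The same doctor records the symptom, and the criterion does nothing about coding out, so this is a partial safeguard.
- *The magnitudes.* They rest on assumed shares and the least favourable composition. This stands, and they should be read only as bounds.
- *The subgroup.* A reader might infer that the upper/lower label follows the biomarker result. No passage says this: the test is presented as separating bacterial from viral infection and guiding prescribing. The supported statement is narrower, namely that the same unblinded doctors assign the label after randomisation. That calls for caution, not for dropping the test.
- *The SAP.* It is not available here and may contain checks. The claim is therefore about the analyses the Protocol names, not that no check exists.
- *The all-visit analysis.* It is diluted and subject to variation in non-ARI prescribing, so a null result could not separate labelling drift from dilution. This stands and limits its role.
- *Generality.* Open-label case identification is common in pragmatic prescribing trials, and the lack of blinding is disclosed. Disclosure does not remove the bias, and training and audit in one arm sharpen it.

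**Conclusion.** The concern holds as a risk of differential case identification that the Protocol, as written, leaves unchecked. Who enters the primary denominator is decided after allocation, by unblinded doctors, under conditions that differ by arm in ways bearing on the diagnosis. The documents show the route. They do not show that labelling will shift, in which direction, or by how much.

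On assumed shares, with no true effect at the planned 50% control rate, a 10% shift yields at most 5.6 points (coding out) or 4.5 points (coding in), which is over a third of the planned 12.5. Mixed recoding gives less. The upper/lower issue affects only the interpretation of that subgroup. The matter should be dealt with before data are analysed, but it does not call for a change to the primary outcome, the sample size or the intervention.

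**What to change.** In the Data analysis plan, or in the SAP with a reference from it, pre-specify:

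1. A by-arm comparison of ARI-coded visits as a share of all outpatient visits, adjusted for each clinic's previous-year value. The previous-year prescription data are already obtained to verify cluster eligibility.
2. A supportive GEE analysis of antibiotic prescriptions over all outpatient visits. State that dilution makes it supportive only: about 3.3 points if ARI is about 26% of visits, a share that is the ratio of two eligibility minimums and should be replaced by the observed one.
3. For type of ARI, keep the subgroup analysis, report the upper/lower mix by arm, and state that its heterogeneity test is read with caution because the label is assigned after randomisation by the same doctors.

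Items 1 and 2 belong together, since offsetting coding in and out would leave the ARI share unchanged.

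The cost is an extract of all visits during follow-up and a little more analysis work.
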